**Method:**

One hundred twenty-eight persons with autism and suicidal and/or self-harming behaviour will be recruited from specialised mental healthcare services and randomised into two conditions: 1) the DBT condition in which the participants have weekly individual cognitive behavioural therapy sessions and a 2.5 h skills training group session twice per week during 6 months, and 2) the treatment as usual condition which consists of weekly individual therapy sessions of 30–45 min with a psychotherapist or social worker. Assessments will take place at baseline, at post-treatment (6 months), and after a follow-up period of 12 months. The mediators will also be assessed at 3 months. The primary outcome is the level of suicidal ideation and behaviour. The secondary outcomes are anxiety and social performance, depression, core symptoms of ASD, quality of life, and cost-utility. Emotion regulation and therapeutic alliance are hypothesised to mediate the effects on the primary outcome.

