### Study interventions

The therapy consists of DBT skills training [46], individual cognitive behavioural therapy [47], and weekly meetings with the consultation team for all trainers and therapists for 1 h. The complete staff will be supervised once a month by a fully certified trainer and supervisor ([name]).

Two adaptations were made to the standard DBT program for this study protocol. First, the telephone consultation (if needed) was limited to the therapist’s availability, which means that not all patients could use 24-h consultation. Second, the treatment period is limited to half of the original treatment time (1 year) because of the expected reduced concentration span. The preference for repetitive instructions in people with ASD, in combination with the concentration span, led to the decision to offer the skills training twice a week [48].

Individual cognitive behavioural therapy will take place on a weekly basis. The order and topics of each session are pre-determined based on Linehan’s hierarchy [15, 16]: suicidal and self-destructive behaviour, therapy interfering behaviour, quality of life interfering behaviour, and generalisation of the skills taught in the training. Each therapy session starts with self-report diary cards [49] that describe problematic behaviours and behaviours that influence the primary goals such as alcohol and drug use, the urge to self-harm, substance abuse, dissociation, level of applied skills, etc. Two skills training groups will take place each week. The skills taught are self-regulation skills, change skills, self-acceptance and acceptance of others, mindfulness, interpersonal effectiveness, and skills to cope with crises. When a meeting is missed, the participant will be asked to catch up by watching video recordings that are made of all the trainings sessions. The therapists keep track of self-reported watching by the experimental subjects. We consider that being in the programme for 5 months is the minimum number of sessions required for an adequate amount of intervention. All therapists are either psychologists or psychiatrists and skill trainers are psychologists, registered nurses, or social workers (*n* = 28). They will have 5 days of training in DBT by a licensed DBT therapist, teacher, supervisor, and trainer (AH).

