The control group will receive treatment as usual. This can be any form of treatment for suicidality in autism which is common within mental health care and is delivered in weekly sessions of 30–45 min with a psychotherapist or social worker. Therapists will only participate in one of the conditions.

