### Sample size

To find an expected medium effect size of 0.50 with an alpha of 0.05 and power of 0.80, our studies requires 128 participants with 64 in each arm. The three participating mental health centres have four sites with mental health services and care for more than 3000 ASD patients. Estimates of suicide ideation and attempts in the population with ASD range from 20.4 to 10%, respectively [2]. If the prevalence of suicidal behaviour is 15%, then the participating centres have 450 eligible patients. A 30% recruitment rate will be enough for the needed 128 participants.

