### Data analysis

The result of randomization will be checked by comparing baseline sociodemographic and clinical parameters between DBT and TAU condition, using univariate analyses. The study is intention-to-treat. So, all patients that have been randomized, will be in the analysis. If patients miss measurements, this will be dealt with LMM that uses expectancy maximisation to impute missing data. If patients miss four sessions in a row, the patient is considered a treatment dropout and therapists will stop pursuing the patients to continue treatment. Treatment drop-out will still be contacted for measurements, though. Treatment dropouts will still be part of the analysis in the intention-to-treat analysis. Study dropouts that have missing measurements will have the LMM imputation strategy to estimate scores and impute these bases on expectancy maximisation. If *p*-values are marginally, we will also use LOCF, last observations carried forward, as an imputation strategy to do a conservative sensitivity analysis. The primary outcome on the suicidality measures will be analysed using Linear Mixed Models (LMM) where condition is the fixed effect, measurement moment and site is a fixed factor, individual is a random effect with the baseline value as a covariate. The group x moment interaction will be assessed for post-treatment and follow-up results. We are aware that the SIDAS is used both in selection of patients and as an outcome measure and that regression to the mean may negatively impact on the interaction effect. The SIDAS score will probably not regress to normal score levels and cause a bottom effect. To cope with the regression to the mean, we compute the main effects of condition and time and the interaction of condition x time with baseline as a covariate. To identify mechanisms of change and the strength of the factors involved, both multilevel models and structural equation models will be used for mediation analyses. Mediation analysis with a multiple mediator model (multiple mediators in the same model) will be calculated with 5000 bootstraps using the PROCESS macro published by Hayes and Rockwood (2017) [58]. Moderators will be analysed using mixed modelling, in addition to the effectiveness analysis. Cost-utility analysis will also be performed.

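### The primary mixed model has no term for the DBT skills groups, so if outcomes are correlated within groups, the standard error of the condition effect is too small

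*Protocol article*

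**What the plan says.** **Model.** In Data analysis, the primary outcome is analysed by a linear mixed model with condition as a fixed effect and "measurement moment and site is a fixed factor, individual is a random effect with the baseline value as a covariate". On testing, the same section says "we compute the main effects of condition and time and the interaction of condition x time with baseline as a covariate". Multilevel models appear there again only for mediation.

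**Delivery.** The abstract gives DBT as weekly individual sessions plus "a 2.5 h skills training group session twice per week during 6 months". Study interventions adds "Two skills training groups will take place each week", without a group size and without saying whether groups are closed or have rolling entry. The abstract describes TAU as weekly individual sessions. Study interventions allows any usual form of treatment in TAU and adds "Therapists will only participate in one of the conditions".

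**Sample size.** The target of the calculation is given as "To find an expected medium effect size of 0.50 with an alpha of 0.05 and power of 0.80". Its result follows in the same sentence: "our studies requires 128 participants with 64 in each arm". No allowance for clustering is mentioned.

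**The concern.** Members of a skills group share trainers, fellow members and group climate. If this makes their outcomes more alike, the mean of the DBT arm varies more than 64 independent patients would imply. The stated model treats patients as independent given site. A fixed site effect is common to both arms, so it cannot represent variation between skills groups within the DBT arm.

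The quantity at stake is the one that Hypothesis 1 needs: the difference between arms at 6 months, sustained at 12. An understated standard error makes its interval too narrow and a false claim of efficacy more likely.

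**Working it through.** **Inputs from the article.** Standardised difference 0.50, alpha 0.05, power 0.80, 64 per arm (Sample size); four sites (Sample size); individual as the only random effect (Data analysis).

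**Assumed, because not stated.** Group size m from 4 to 16; ICC from 0.01 to 0.15; equal total variance in both arms; clustering in the DBT arm only.

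**Step 1: the article's own figure.** A two-sided two-sample t-test gives 63.77, rounded up to 64 per arm, 128 in total. Power at 64 per arm is 0.801 (t) or 0.807 (normal). A one-sided test would need 50 per arm. So 128 is a two-sided calculation on independent patients, with no clustering allowance hidden in it.

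**Step 2: effect of ignoring the groups.**
- Design effect in the DBT arm: DE = 1 + (m − 1) × ICC.
- True over model variance of the difference: V = (1 + DE)/2.
- Standard error ratio: √V.
- Actual type I error: 2 × [1 − Φ(1.96/√V)].
- Power if the clustering is modelled (normal approximation): Φ(0.50/√((1 + DE)/64) − 1.96).

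For m = 8 and ICC = 0.05: DE = 1 + 7 × 0.05 = 1.35; V = 2.35/2 = 1.175; √V = 1.084; 1.96/1.084 = 1.81; type I error 7.1%.

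| m | ICC | DE | V | SE ratio | Type I error | Power, clustering modelled |
|---|---|---|---|---|---|---|
| 4 | 0.01 | 1.03 | 1.015 | 1.007 | 5.2% | 0.802 |
| 4 | 0.05 | 1.15 | 1.075 | 1.037 | 5.9% | 0.779 |
| 4 | 0.10 | 1.30 | 1.150 | 1.072 | 6.8% | 0.751 |
| 8 | 0.01 | 1.07 | 1.035 | 1.017 | 5.4% | 0.794 |
| 8 | 0.05 | 1.35 | 1.175 | 1.084 | 7.1% | 0.742 |
| 8 | 0.10 | 1.70 | 1.350 | 1.162 | 9.2% | 0.682 |
| 16 | 0.05 | 1.75 | 1.375 | 1.173 | 9.5% | 0.674 |
| 16 | 0.10 | 2.50 | 1.750 | 1.323 | 13.8% | 0.571 |
| 16 | 0.15 | 3.25 | 2.125 | 1.458 | 17.9% | 0.492 |

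**Step 3: does the fixed site term help?** Simulation with four fixed sites, a baseline covariate, two follow-ups and no group term (6,000 runs per setting) gave these rejection rates under no treatment effect:

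| m | ICC | Condition effect at 6 months | Condition effect, averaged | Condition × time, 6 v 12 months |
|---|---|---|---|---|
| 8 | 0 | 5.2% | 5.1% | 4.9% |
| 8 | 0.05 | 7.1% | 7.7% | 5.1% |
| 8 | 0.10 | 9.1% | 10.7% | 4.7% |
| 16 | 0.10 | 15.0% | 17.5% | 5.0% |

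The site term does not remove the inflation. The averaged effect is hit harder because averaging reduces occasion noise but not the group effect. The simulation split residual variance evenly between person and occasion (0.5 and 0.5), so the average has variance 0.5 + 0.25 = 0.75, and an ICC of 0.05 becomes 0.05/0.75 = 0.067. The 6- versus 12-month contrast stays near 5% because a group effect that is constant over time cancels in the difference.

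**The case against.** **The inflation is conditional.** It needs a positive within-group ICC, and the article gives neither ICC nor group size. With small groups and a small ICC it is negligible (5.2% at m = 4, ICC 0.01). This stands, and no single error rate can be asserted for this trial.

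**Group size.** Because the Randomisation section uses blocks of 16 with 8 per arm, a reader might infer groups of 8. Nothing links an allocation block to a therapy group; 8 is only illustrative here.

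**Closed groups.** A reader might infer that the same patients stay together for 6 months. The article does not say so. Patients are randomised individually over about two years (Trial status), so rolling entry is possible. DBT also includes individual therapy, and missed meetings are made up by video. These points may lower the correlation and complicate the definition of a cluster, but they do not show it to be zero.

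**Scope.** A reader might extend the point to every secondary analysis and to every test of the primary outcome. Data analysis states this model for the primary outcome only, and the 6- versus 12-month interaction is largely spared if the group effect is constant. Neither extension is supported.

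**Clustering in TAU.** Therapists are nested within arm, and TAU may take any usual form, so some clustering by therapist is possible in both arms. It was not quantified.

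**A condensed article.** A fuller plan might add a group term. But the article does not leave the random part open: it names one random effect, which does not fit the delivery it describes.

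**Conclusion.** The point holds in conditional form. The stated primary model omits a source of dependence that the design creates in the DBT arm, and the fixed site effect does not absorb it. For any positive within-group ICC, the standard error of the condition effect at 6 months, at 12 months or averaged is too small.

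The size rests on assumptions: a type I error of about 5.2% to 18% across the range examined, and about 7% to 9% for groups of 8 at ICC 0.05 to 0.10. The document does not support a flat statement that the trial's error rate exceeds 5%, or by how much. Confidence is high in the omission and the direction, and low in any one figure.

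**What to change.** 1. Record skills-group membership, with dates, for each DBT participant. The article reports data collection as ongoing, so this can start now.
2. Pre-specify a partially nested mixed model for the primary outcome: the stated terms, plus a random skills-group effect in the DBT arm only, arm-specific residual variance, and Satterthwaite or Kenward-Roger degrees of freedom.
3. If groups have rolling entry, define the cluster as the site's skills group or cohort period, or use a multiple-membership term. With four sites, one cluster per site would leave only four clusters and very few degrees of freedom.
4. Add a therapist random effect as a sensitivity analysis.
5. Use the same structure for any secondary outcome analysed by a mixed model.
6. State the assumed group size and ICC, and the resulting power.

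**Cost.** One recorded variable and a change of model wording; intervals become wider. At m = 8 and ICC 0.05, power at d = 0.50 is about 0.74 by the normal approximation, and about 0.70 in a simulated group-mean test with Satterthwaite degrees of freedom on 8 groups. With that test, power is about 0.77 even at ICC 0, because degrees of freedom are lost. It restored the type I error to about 5%; the mixed model proposed here was not itself simulated. By the normal approximation, keeping the planned power at m = 8 would take 2 × ⌈64 × 1.175⌉ = 152 participants at ICC 0.05, or 2 × ⌈64 × 1.35⌉ = 174 at ICC 0.10. If recruitment stays at 128, the lower power should be stated.

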### Objectives

#### Primary objective

The primary objective of this study is to determine the efficacy of DBT treatment in persons with ASD on suicidal and/or self-harming behaviour.
► *Hypothesis 1*: DBT treatment is effective in decreasing suicidal and/or self-harming behaviour in the persons with ASD as measured by the combined score on Suicidal Ideation Attributes Scale (SIDAS) [30] and Lifetime Parasuicide Count (LPC) [31] in the first 6 months of treatment, compared to treatment as usual (TAU), and that this difference between the groups is sustained at 12 months.

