## Methods/design

### Design

This study is a single-blind multicentre randomised controlled trial with two arms: dialectical behavioural therapy (DBT) versus treatment as usual (TAU). TAU consists of weekly sessions of 30–45 min with a psychotherapist or social worker. The two groups will be compared at baseline, post-treatment (6 months), and at follow-up (12 months). The mediators will also be assessed mid-treatment at 3 months. All analyses will be performed according to the intention-to-treat principle. This trial meets all the requirements of the SPIRIT Protocol Checklist which provides guidance for protocols of clinical trials [41]. Checklist is provided in Additional file 1.

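### Fitted as written, the primary mixed model assumes one variance for 6 and 12 months; letting the variance differ by moment protects the two condition contrasts that Hypothesis 1 needs, for one extra parameter

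*Protocol article*

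**What the plan says.** All references are to the protocol article.

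- **Data analysis, fixed part.** In the linear mixed model for the primary outcome, "condition is the fixed effect, measurement moment and site is a fixed factor".
- **Data analysis, random part.** "individual is a random effect with the baseline value as a covariate". No other random term, and no covariance structure for the residuals, is given.
- **Data analysis, terms examined.** "The group x moment interaction will be assessed for post-treatment and follow-up results". In answer to regression to the mean, the section adds: "we compute the main effects of condition and time and the interaction of condition x time with baseline as a covariate".
- **Primary objective, Hypothesis 1.** Treatment is to lower the combined suicidality score "in the first 6 months of treatment, compared to treatment as usual (TAU), and that this difference between the groups is sustained at 12 months".
- **Design.** "The two groups will be compared at baseline, post-treatment (6 months), and at follow-up (12 months)". With baseline used as a covariate, the responses are the 6- and 12-month scores.
- **Sample size.** 128 participants, 64 per arm, for an "expected medium effect size of 0.50 with an alpha of 0.05 and power of 0.80". The article gives no standard deviation at any moment.

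**The concern.** A participant effect plus independent residuals of equal variance is compound symmetry: one variance for both moments and one covariance between them. The standard error of the condition contrast at 6 months and that at 12 months are then both built on the average of the two true variances.

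This matters because of how Hypothesis 1 is framed. It has two parts, an effect at 6 months and a difference still present at 12 months. An interaction that is not significant does not show an effect at either moment, and an effect averaged over moments does not show that it lasts. The hypothesis therefore rests on the two separate contrasts, which are the quantities exposed to a wrong common variance. At the moment with more spread, the standard error is too small and false positives are too frequent. At the other it is too large and power is lost. Which moment gains and which loses cannot be known in advance.

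**Working it through.** **Inputs from the article.** 64 per arm, standardised effect 0.50, alpha 0.05, power 0.80; responses at 6 and 12 months; participant as the only named random effect. Sidedness is not stated.

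**Reproducing the planned size.** A two-sided two-sample t-test with effect 0.50 and power 0.80 needs 63.77 per arm, hence 64 per arm and 128 in all, with power 0.801. A one-sided test would need 50 per arm, so the plan is two-sided. This calculation compares two groups and does not use the mixed-model covariance.

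**Assumed input.** The ratio k of the larger to the smaller variance across the two moments. The article gives no basis for a value, so a range is shown.

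**Closed form, complete data.** Let the variances be v6 and v12, the covariance c, and the average v = (v6 + v12)/2.

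- True SE of the contrast at moment t: sqrt(2·v_t/64). SE under the common-variance model: sqrt(2·v/64).
- Ratio of model SE to true SE: R = sqrt(v/v_t).
- Actual type I error: 2·(1 − Φ(1.96·R)).
- Power where the correct analysis has 80%: 1 − Φ(1.96·R − 2.80).

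Setting the smaller variance to 1 and the larger to k gives v = (1 + k)/2.

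| k | R, more variable moment | Type I error there | R, other moment | Type I error there | Power there |
|---|---|---|---|---|---|
| 1 | 1.000 | 5.0% | 1.000 | 5.0% | 80% |
| 1.25 | sqrt(1.125/1.25) = 0.949 | 6.3% | sqrt(1.125) = 1.061 | 3.8% | 76% |
| 1.5 | sqrt(1.25/1.5) = 0.913 | 7.4% | sqrt(1.25) = 1.118 | 2.8% | 73% |
| 2 | sqrt(1.5/2) = 0.866 | 9.0% | sqrt(1.5) = 1.225 | 1.6% | 66% |

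On the standard deviation scale, a 12-month to 6-month ratio between 0.9 and 1.1 keeps type I error between about 3.8% and 6.2%.

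**Why the interaction and the average escape.** The change between moments has variance v6 + v12 − 2c, and compound symmetry gives 2v − 2c, the same number. The mean of the two moments has variance (v6 + v12 + 2c)/4, and compound symmetry gives (2v + 2c)/4, again the same. Only the separate moments are misjudged.

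**Check by fitting the model.** REML fits to 2,000 simulated trials per scenario, with 128 participants, two moments, four sites and a baseline covariate. Residual correlation 0.6 and baseline slope 0.5 were assumed. At a standard deviation ratio of 1.25 (variance ratio 1.25² = 1.56), with complete data:

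| Quantity | Rejection, common variance | Rejection, unstructured |
|---|---|---|
| 6-month contrast | 2.1% | 4.3% |
| 12-month contrast | 6.9% | 3.8% |
| Interaction | 4.2% | 4.2% |
| Averaged effect | 4.4% | 4.6% |

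The closed form gives 2.7% and 7.6% for the two contrasts under a common variance. Model and empirical standard errors show the same pattern. Common variance gives 0.203 at both moments, against empirical values of 0.177 (6 months) and 0.222 (12 months). Unstructured gives 0.179 and 0.223. With assumed dropout of 10% by 6 months and 25% by 12 months, rejection for the interaction is 5.8% against 5.6%.

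**Price when the variances are in fact equal.** With a residual-scale effect of 0.5 and complete data, power is 0.774 (unstructured) against 0.773 at 6 months, and 0.779 against 0.777 at 12 months. With the same dropout it is 0.759 against 0.758, and 0.700 against 0.699.

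**The case against.** The strongest objection is that the article never commits to equal variances. It does not call the participant effect a random intercept, does not say that nothing else enters the covariance, and does not say that the residuals are homogeneous. A reader might infer that the plan forces compound symmetry. It does not: a participant effect with moment-specific residual variances fits the same words, and it reproduces any 2x2 covariance whose off-diagonal term is non-negative and no larger than either variance. A journal article may also leave the residual structure to a fuller document that is not shown. This stands. The point is about what the listed model does when fitted as listed, not about a proven error.

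Second, a reader might infer that the whole primary analysis is compromised. That is not supported. The terms the Data analysis section names, the interaction and the main effect of condition, keep correct standard errors with complete data. The exposed contrasts become necessary through Hypothesis 1, not through a test named in that section.

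Third, the wording about a main effect of time might suggest that baseline is also a response, with its spread cut by the entry threshold. The section twice makes baseline a covariate, and a time effect can be estimated from 6 and 12 months alone. That reading is speculative and is not relied on.

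Finally, the size of the error depends on an unknown ratio, and for nearly equal spreads it is slight. This also stands. Equal variance, however, is no better supported by the article than unequal variance.

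**Conclusion.** The concern holds in limited form, as an improvement that costs almost nothing. Taken at its most natural reading, the listed model ties the 6- and 12-month variances together, and the two contrasts that Hypothesis 1 requires then have standard errors that err in opposite directions whenever the spread changes. The figures run from no error at equal variances to 9.0% type I error at one moment and 66% power at the other when the variance doubles. They assume complete data, homogeneous residuals, 64 per arm and variance ratios that the article does not supply. The planned sample size of 128 is not affected.

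**What to change.** Keep the stated fixed effects and the baseline covariate. State that only the 6- and 12-month scores are responses. Then do one of the following:

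- replace the random intercept with an unstructured 2x2 covariance by participant; or
- keep the participant effect and allow a separate residual variance at each moment.

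Do not combine a participant effect with an unstructured residual: that has four parameters for a matrix with three, and cannot be identified. Report the condition contrast at 6 and at 12 months, with confidence intervals, from the chosen model.

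The cost is one variance parameter (three instead of two), with no new data and no change in sample size. A baseline by moment term and Kenward-Roger degrees of freedom are optional and are not needed to correct this problem. The Trial status section reports that data are still being collected, so the choice can be fixed before analysis. If a fuller analysis plan already lets the variance differ by moment, a reference to it closes the point.

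### Baseline entered with a single slope cancels from the condition × time interaction, so it cannot be the stated remedy for regression to the mean; adding baseline × moment is a free improvement

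*Protocol article*

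**What the plan says.** The Data analysis section of the protocol article describes a linear mixed model with condition, measurement moment and site as fixed terms, in which "individual is a random effect with the baseline value as a covariate". The condition × moment interaction is to be assessed for the post-treatment and follow-up results.

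The section then notes that the SIDAS both selects patients and measures the outcome, and that "regression to the mean may negatively impact on the interaction effect". Its answer is that "we compute the main effects of condition and time and the interaction of condition x time with baseline as a covariate". The model is thus described twice, and both times the only interaction named is condition × time.

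The primary hypothesis (Primary objective) is an arm difference over the first 6 months and that "this difference between the groups is sustained at 12 months". The Sample size section states that "our studies requires 128 participants with 64 in each arm". It gives no correlation between baseline and later scores, and no dropout rate.

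**The concern.** The section names a threat to one particular effect, the condition × time interaction, and offers a covariate as protection. A covariate with one slope shifts the 6- and 12-month scores by the same amount for each patient. An interaction between those moments is a difference between them, so the shift vanishes. The remedy does not reach the effect it is offered for.

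Two things are at stake. The first is the rationale: a reader would believe that the interaction has been adjusted for baseline when it has not. The second is the 12-month contrast, which carries the sustained-effect half of Hypothesis 1. A common slope adjusts it with a value pooled over both moments. If that value is wrong for month 12, and the patients still observed at month 12 differ in baseline severity between arms, the contrast is adjusted by the wrong amount.

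**Working it through.** **Inputs from the article.** Effect size 0.50, alpha 0.05, power 0.80, 64 per arm (Sample size); assessments at baseline, 6 and 12 months (Design); the model terms quoted above (Data analysis).

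**Assumed, because the article gives no values.** Unit-SD outcome; true effect −0.50 at both moments; baseline slope 0.6–0.7 at 6 months and 0.2–0.6 at 12 months; 6-to-12-month correlation 0.5–0.6; missingness of 10–30% at 12 months only, with log odds of 1 per SD of baseline where it depends on baseline. Site was left out of the simulations.

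**Plan's own figure.** The normal approximation gives n per arm = 2(1.960 + 0.842)²/0.50² = 62.8, so 63. The exact two-sided t-test gives 63.8, so 64 per arm and 128 in total, with power 0.801. The stated N is reproduced.

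**Step 1: cancellation.** Write the model as

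Y(i,t) = μ(t) + τ(t)·Z(i) + β·B(i) + site + u(i) + e(i,t), t = 6, 12.

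Subtracting the two moments within a patient gives

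Y(i,12) − Y(i,6) = [μ(12) − μ(6)] + [τ(12) − τ(6)]·Z(i) + e(i,12) − e(i,6).

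β·B(i) is gone, along with site and u(i). With complete data the interaction estimate is the raw arm difference in mean change. In one simulated trial of 64 per arm it was 0.1372 without baseline, 0.1372 with baseline and 0.1372 as the raw difference, with SE 0.1400 both ways. Counting baseline as a third outcome moment does not rescue the remedy, because the same subtraction applies to each contrast between moments.

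**Step 2: what the covariate does do.** In the same check the SE of the 12-month contrast fell from 0.159 without baseline to 0.143 with it.

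**Step 3: regression to the mean.** With patients selected on high baseline, the between-arm interaction stayed at about 0 and the arm difference in change from baseline to 12 months stayed at −0.50. Both arms regress alike.

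**Step 4: chance imbalance.** If the true slopes are β6 and β12, the unadjusted interaction carries (β12 − β6) × (arm difference in mean baseline). That difference has SD √(2/64) = 0.18. For slopes 0.2 to 0.4 apart, the shift is typically 0.2 × 0.18 = 0.04 to 0.4 × 0.18 = 0.07 SD. It is zero if the slopes are equal. Over repeated randomisation this is added variance and not bias.

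**Step 5: bias of the 12-month contrast.** Roughly, bias ≈ (β12 − β pooled) × D, where D is the arm difference in mean baseline among those observed at 12 months. Both factors must be non-zero. Large-sample results (400,000 per arm) for the common-slope model, in SD units, where positive means toward the null:

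| Slopes 6 → 12 months | Same pattern both arms, 20% / 30% | Same dependence, 10% vs 30% (more in DBT) | Baseline-related in DBT only, 20% / 30% | Opposite directions, 20% / 30% |
|---|---|---|---|---|
| 0.6 → 0.6 | 0.002 / −0.004 | 0.000 | −0.002 / 0.000 | 0.001 / 0.000 |
| 0.6 → 0.4 | 0.000 / −0.002 | 0.026 | 0.027 / 0.041 | 0.056 / 0.083 |
| 0.6 → 0.2 | 0.001 / 0.001 | 0.053 | 0.055 / 0.085 | 0.109 / 0.158 |
| 0.7 → 0.3 | −0.001 / 0.001 | 0.049 | 0.053 / 0.078 | 0.101 / 0.152 |

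With baseline × moment added, no bias exceeded 0.006 in size. The sign follows D: it is toward the null here because DBT is assumed to lose more of the severe patients, and it reverses if TAU does.

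**Step 6: at the planned size.** With 64 per arm, 3,000 replicates and dropout of 10% vs 30%:

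- Slopes 0.6 → 0.4: mean estimate −0.475 with the common slope and −0.501 with baseline × moment; power 0.785 and 0.831; coverage 0.928 and 0.933.
- Slopes 0.6 → 0.2: mean estimate −0.458 and −0.508; power 0.703 and 0.799; coverage 0.915 and 0.921.

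**The case against.** The strongest defence is that the single slope is read from silence. The article neither excludes a baseline × moment term nor claims to be the full plan, and a fuller protocol or SAP may contain one. That would dispose of a complaint about missing detail. It does not dispose of this one, because the article names a purpose and a remedy, and the remedy as described fails that purpose. It does lower the confidence with which one can say what will be fitted.

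The defence also rightly says that the interaction needed little protection. Randomisation equalises regression to the mean, and Hypothesis 1 is naturally tested by contrasts at each moment, where baseline does not cancel. Both points stand.

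A reader might infer more than the article supports:

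- **That the 12-month contrast is biased whenever dropout depends on baseline severity.** It is not. With the same pattern in both arms, or with equal slopes, the bias was nil. The article reports neither unequal slopes nor unequal dropout, and patients who stop treatment are still to be approached for assessment, which limits missing data.
- **That the covariate is useless.** Step 2 shows otherwise.
- **That chance imbalance stays in full in the interaction.** It enters only through the slope difference.
- **That expecting scores to regress shows the slopes to be unequal.** A fall in the mean is absorbed by the moment effect and says nothing about slopes.

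**Conclusion.** The point holds in a limited form. As written, baseline cancels exactly from the condition × time interaction with complete data, so it cannot be the remedy for regression to the mean in that interaction. This part is algebra and depends only on the one-slope reading.

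The further consequence is conditional. The 12-month contrast is biased only when the baseline slope changes between 6 and 12 months and baseline-related dropout also differs between arms. Under the assumed values the size is about 0.02 to 0.09 SD toward the null, which is 4% to 18% of the planned effect of 0.50 (0.02/0.50 and 0.09/0.50). About 0.16 SD arises only when dropout runs in opposite directions in the two arms, an extreme case. Coverage barely moves. The slopes, correlations and dropout rates are all assumptions.

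The fault lies more in the stated rationale than in the validity of the comparison. It is a free improvement.

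**What to change.** In the Data analysis section, specify the baseline value and baseline value × moment (6 and 12 months) as covariates. Take the condition contrasts at 6 and 12 months, and any condition × moment test, from that model.

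Replace the regression-to-the-mean rationale: randomisation makes regression to the mean equal between arms on average, while the baseline terms improve precision, adjust for chance imbalance and allow for dropout related to baseline.

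The cost is one degree of freedom among 128 patients and a line or two of text. It needs no new data and no change in sample size, and nothing material is lost if the two slopes prove equal. If a fuller plan already contains the term, only the rationale needs correcting.
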